#### Body composition assessment

Body fat percentage and distribution will be assessed by bioelectrical impedance analysis (BIA) (Tanita BC-418, Illinois, USA).

#### Physical activity assessment

Physical activity will be measured by the International Physical Activity Questionnaire (IPAQ) comprising seven questions translated by Iran's National Elites Foundation; overall physical activity will be reported as Metabolic Equivalent Task minutes per week (MET-min/wk), calculated as follows: [26]Walking MET-minutes/week = 3.3 * walking/minutes per day * number of days per week spent on walking was reported.Moderate MET-minutes/week = 4.0 * moderate intensity/minutes per day * number of days per week spent on moderate intensity activityVigorous MET- minutes per week = 8.0 * Vigorous intensity/minutes per day * number of days per week spent on vigorous intensity activityTotal physical activity MET-minutes/week = Walking + Moderate + Vigorous MET minutes/week scores

#### Sun exposure assessment

Sun exposure will be determined by a questionnaire designed for this purpose. Participants will be asked to report hours per week spent outdoor activity, and body surface area (BSA) exposed to sunlight while outdoors. The total percentage of BSA exposed to sunlight will be calculated as the sum of the reported percentage of BSA exposed reported for each part of the body by subjects. BSA will be regarded as follows: 9% for face, 1% for each hand, 9% for each arm, and 18% for each leg. Some parts of the body including chest waist and abdomen will not be considered in the total BSA calculation.

A sun exposure index will be finally calculated by multiplying the percentage of BSA exposed by the hours of exposure to sunlight per week [27].

#### Dietary intake assessment

A twenty-four-hour recall for three days, including a weekend day and two working days, will be used to assess dietary intakes at the beginning and end of the study. Participants will be asked to record the total consumption of foods, beverages, and supplements during 24 h based on standard household measures, including tablespoons and cups; they will be given a leaflet describing detailed instructions on recording their intakes.

### Laboratory assessment

#### Blood sampling

Fasting venous blood samples (15 ml) will be taken in spring (April–May) and winter (February–March) from all participants in a sitting position by phlebotomy. Blood sample will be divided in two tubes: (1) a plastic tube with an anticoagulant, EDTA (Ethylenediaminetetraacetic acid); (2) a plastic tube with an anticoagulant, EDTA and anti-protease. Blood collection tubes will be tagged with identification codes; the tubes containing the EDTA blood sample will be centrifuged at 3000×*g* for 10 min for white blood cell (WBC) separation, while the tubes containing EDTA and anti-protease blood sample will be centrifuged for plasma separation. Obtained plasma will be distributed in clean micro-tubes and will be kept at − 80 °C until the day of analysis. White blood cells will be transferred to clean micro-tubes in aliquots, and they will also be kept at − 80 until the day of examination.

#### DNA extraction

DNA will be extracted from WBC using the DNA Blood Kit. To determine DNA concentration, spectrophotometric absorbance of the samples at 260 nm and 280 nm will be measured using a Nanodrop spectrophotometer thermo scientific. DNA quality will then be determined by the A260/A280 ratio, and an A260/A280 ratio of 1.7–2 will be considered as good quality DNA. Extracted DNA will subsequently be stored at − 20 °C for the following PCR amplification of and restriction fragment length polymorphism (RFLP) and Tetra-amplification refractory mutation system (ARMS) PCR.

#### DNA genotyping

Polymerase chain reaction (PCR)-RFLP methods will be used for *VDR* genotyping at FokI, ApaI, TaqI, BsmI SNPs, and tetra-primer ARMS-PCR method for Cdx-2. Initial PCR amplification will be performed in a total volume of 50 μl containing 100–300 ng of genomic DNA, 1 pmol of each forward and reverse primer, 25 μl of master mix PCR. DNA samples will be amplified using T100 thermal cycler with cycling parameters as follows: initial denaturation at 95 °C for 5 min, 30 cycles at 94 °C for 45 s for denaturation, 45 s at 60 °C for annealing, and 60 s at 72 °C for extension, will be followed by 7 min at 72 °C for final extension and cooling at 12 °C for 10 min. Two percent agarose gel electrophoresis will be conducted to determine the accuracy of amplified fragment of DNA.

FokI, ApaI, TaqI, BsmI polymorphisms of the *VDR* gene will be detected by RFLP as follows:

Fok1: RFLP will be performed in 40-μl mixture containing 1 μl of restriction endonuclease FokI, 2 μl 10X buffer FokI, 17 μl nuclease-free water, and 10 μl amplified PCR product. The incubation temperature will be adjusted based on the manufacturer's instructions for the restriction endonuclease Fok1.

ApaI: RFLP will be carried out in a tube containing 2 μl of restriction endonuclease ApaI, 2 μl 10X buffer ApaI, 18 μl nuclease-free water, and 10 μl amplified PCR product. The incubation temperature will be adjusted based on the manufacturer's instructions for the restriction endonuclease ApaI.

TaqI: RFLP will be performed in a micro-tube containing 1 μl of restriction endonuclease TaqI, 2 μl 1X buffer TaqI, 18 μl nuclease-free water, and 10 μl amplified PCR product. The incubation temperature will be maintained based on the manufacturer's instructions for the restriction endonuclease. Micro-tubes will completely be sealed with parafilm to avoid evaporation.

BsmI: RFLP will be performed in 40-μl mixture containing 1 μl of restriction endonuclease BsmI, 2 μl 1X buffer BsmI, 18 μl nuclease-free water, and 10 μl amplified PCR product. The incubation temperature will be maintained based on the manufacturer's instructions for the restriction endonuclease.

Digested products will be resolved on a 3% agarose gel containing 0.5 μg/mlTBE 0.5X using a gel electrophoresis system at 100 V for 90 min. The gel will be visualized under UV light using Gel Documenting system.

Cdx2 polymorphism of *VDR* will be determined using tetra-primer ARMS-PCR. The genomic DNA will be amplified by four primers in a single PCR carried out in a total volume of 50 μl, containing 100–300 ng of genomic DNA, 25 μl of master mix PCR, and 1 pmol/μl of each primer followed by electrophoresis. The 3′ end of two primer pairs will be specified to G allele and the other for A allele.

Sequencing of 10% of samples will be carried out to validate the accuracy of genotype scoring by RFLP-PCR and tetra-primer ARMS-PCR.

#### Biochemical assay

Lipid profiles including plasma total cholesterol (TC), low-density lipoprotein cholesterol (LDL-C), high-density lipoprotein cholesterol (HDL-C), triglycerides (TG), alanine aminotransferase (ALT), and aspartate aminotransferase (AST) will be measured using the enzymatic calorimetric method. Plasma 25(OH)D concentrations will be measured by ELISA kit.

#### Inflammatory biomarker measurement

Plasma inflammatory markers will be evaluated by measuring plasma interleukin 6 (IL6), tumor necrosis factorα (TNFα), human high sensitivity C-reactive protein (hs-CRP), and interferon β (IFNβ) levels.

#### Oxidative stress assessment

Oxidative stress will be determined by measurement of plasma superoxide dismutase (SOD), total antioxidant capacity (TAC), and malondialdehyde (MDA), using colorimetric method [28, 29].

#### Cell proliferation, differentiation, damage, and apoptosis assessment

Apoptosis will be assessed by determining plasma Bcl2 levels. The 8-hydroxy-2'-deoxyguanosine (8-OHdG) will be measured as DNA damage indicator using ELISA. Also, ELISA method will be implemented to determine plasminogen activator inhibitor-1(PAI-1), E-cadherin, matrix metallopeptidase 9 (MMP9), soluble intercellular adhesion molecule-1 (sICAM-1), and soluble vascular cell adhesion molecule-1 (sVCAM-1) as a proliferation, differentiation, and metastasis status.

### Statistical analyses

We will check the distribution of variables using the Shapiro–Wilk test. The genetic factors, Apa-I, Fok1, Taq-I, Bsm1, and Cdx2, will be considered as the main exposures. To check the within-factor differences in case of normality, we will use one-way ANOVA, and for skewed (non-normal) variables, we will use the Kruskal–Wallis *H* test.

To assess the effect of each category of exposures on outcomes of interest, we will use multiple linear regression. We will log-transform all of the non-normal variables and compute the differences for all response variables (25(OH)D3, BMI, WC, HC, fat mass, TNFα, IL6, hs-CRP, PAI-1, Bcl2, SOD, TAC, MDA, 8-OHdG, MMP9, IFNβ, E-cadherin, sICAM, and sVCAM,) from second and baseline follow-up. All analyses will be adjusted for potential confounders, including energy, fat, carbohydrate and protein intakes, physical activity, sun exposure, and 25(OH)D3 at baseline. The significant effect of the coefficients of different categories of genetic factors will be checked; we will use cluster robust standard errors because of repeated measurements on each subject.

Deviation from Hardy–Weinberg equilibrium for each SNP will be determined using Fisher’s exact test, performing by the HWE exact function in the R package “genetics.” Deviation from Hardy–Weinberg equilibrium for each SNP will be determined using “genhwi” command in Stata. Haplotypes frequencies and distributions will be estimated using the Haplo.em, the haplo.stats software package in the R [30]. The association of haplotypes with outcomes of interest will be tested using the means of the haplo.glm function of the R package “haplo.stats.”

We will use Stata 14.0 (StataCorp. 2015. Stata Statistical Software: Release 14. College Station, TX: StataCorp LP.), and R Statistical software (R Core Team (2017). R: A language and environment for statistical computing. R Foundation for Statistical Computing, Vienna, Austria. URL https://www.R-project.org/.).

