## Objectives

### Primary objectives

To compare plasma 25-hydroxy vitamin D_3_(25(OH) D_3_) within and between polymorphic groups (Fok1, Bsm1, Taq1, Apa1, and Cdx2) in breast cancer survivors, adjusted for potential confounders.To compare plasma 25-hydroxy vitamin 25(OH) D_3_within and between haplotype groups in breast cancer survivors, adjusted for potential confounders.

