#### Intervention

One hundred ninety-eight breast cancer survivors will receive 4000 IU of vitamin D_3_ daily for 12 weeks (cholecalciferol tablets will be manufactured by *JALINOUS PHARMACEUTICAL* CO, Tehran, Iran). Subjects will be given 84 pills at the beginning of the study and will be instructed to consume one tablet with one of their daily meals. Participant compliance will be assessed through biweekly telephone calls. The intervention period will be 12 weeks. Health-related benefits of vitamin D without any increase in the risk of health problems have been demonstrated by plasma 25(OH)D levels of 75–110 nmol/l, achieved through daily supplementation of vitamin D_3_ in the range of 1800–4000 IU [25]. Anthropometric measurement, body composition analysis, dietary, physical activity, and laboratory assessments will be carried out before and after supplementation, and outcomes of interest will be compared between variant *VDR* polymorphic groups.

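### A Shapiro–Wilk result decides whether each outcome is analysed as an absolute or a log change, and no named analysis is assigned the adjusted within-group part of the primary objective

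*Protocol article*

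**What the plan says.** All references are to the protocol article.

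- **Primary objectives.** Plasma 25(OH)D3 is to be compared "within and between polymorphic groups (Fok1, Bsm1, Taq1, Apa1, and Cdx2) in breast cancer survivors, adjusted for potential confounders", and likewise "within and between haplotype groups in breast cancer survivors, adjusted for potential confounders".
- **Intervention.** There are two measurement times: "laboratory assessments will be carried out before and after supplementation". A within-group comparison is therefore each woman's after value against her own before value.
- **Statistical analyses, first paragraph.** Normality comes first: "We will check the distribution of variables using the Shapiro–Wilk test". The SNPs are then named as the factors: "The genetic factors, Apa-I, Fok1, Taq-I, Bsm1, and Cdx2, will be considered as the main exposures". The choice of test follows: "To check the within-factor differences in case of normality, we will use one-way ANOVA, and for skewed (non-normal) variables". For that skewed case the plan's answer is: "we will use the Kruskal–Wallis *H* test".
- **Statistical analyses, second paragraph.** The effect of each genotype category is assessed by multiple linear regression. Non-normal variables are log-transformed and second-minus-baseline differences computed for 19 listed responses. Adjustment is for energy and macronutrient intakes, physical activity, sun exposure and baseline 25(OH)D3. Cluster-robust standard errors are named because subjects are measured repeatedly. Haplotypes go to haplo.glm.

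The section gives no level for the Shapiro–Wilk test and does not say whether it is applied to measured values, changes or residuals.

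**The concern.** There are two separate problems.

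**Scale.** The hypothesis is that response differs by genotype. Whether it does can depend on scale: equal absolute rises from unequal baselines are unequal ratios. Under the stated rule, sample size and chance help to decide which question is answered for each outcome, 25(OH)D3 included. With no control group, the between-genotype contrast carries most of the trial's inference, so its scale should not follow from a preliminary test on the same data. The normality that matters to a regression is also that of its residuals.

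**Within-group part.** The objective asks for an adjusted comparison within groups. The only sentence using the word *within* in the analysis section names tests for independent groups that take no covariates.

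**Working it through.** **Group sizes.** The plan's total reproduces as 55 × 3 × 1.20 = 198. With 20% dropout, 198 × 0.8 = 158.4 complete. Applying the stated Fok1 minor allele frequency of 0.3285 under Hardy–Weinberg proportions:

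- 158.4 × 0.6715² = 71.4
- 158.4 × 2 × 0.3285 × 0.6715 = 69.9
- 158.4 × 0.3285² = 17.1

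Groups of 71, 70 and 17 are used below.

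**Which quantity is logged.** A change can be negative, so the log must be taken of the measured values before differencing. The response is then log(after) − log(before) = log(after/before), a ratio. If normality is not rejected it is after − before.

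**How often the switch fires.** Simulated Shapiro–Wilk rejection at an assumed 5% level (1,000 gamma samples per cell):

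| Skewness | n = 198 | n = 158 |
|---|---|---|
| 0.3 | 0.32 | 0.26 |
| 0.5 | 0.71 | 0.63 |
| 0.7 | 0.95 | 0.90 |
| 1.0 | 1.00 | 1.00 |

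Repeat runs agree to within a few points. The result also depends on sample size: for lognormal data with log-SD 0.2, rejection is 34% at n = 55 and 76% at n = 158. Strong skew is always logged; for mild skew the outcome is uncertain.

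**Why the scale matters.** With hypothetical values, a rise of 40 from 30 and from 60 is the same difference, but 70/30 = 2.33-fold against 100/60 = 1.67-fold.

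**Size in an illustration.** Assumed inputs, none from the protocol: baseline lognormal with median 40, shifted by 5 units per allele; a true rise of 35 (SD 12) in every genotype; groups of 71/70/17; 3,000 simulated trials. Rejection of no genotype difference at 5%:

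| Model | Absolute change | Log change |
|---|---|---|
| No baseline covariate | 0.051 | 0.392 |
| Own baseline as covariate | 0.056 | 0.049 |

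For baseline log-SD from 0.5 to 0.3, the unadjusted log-scale figure runs from 32% to 46%. A covariate unrelated to the marker's own baseline leaves it at 39% (log-SD 0.4). The log-scale rejections are not errors on their own scale, since the ratios do differ; they show that the answer changes with the scale.

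**Which outcomes are exposed.** Of the 19 listed responses, only 25(OH)D3 has its own baseline among the listed covariates. That leaves 19 − 1 = 18.

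**Within-group part, side by side.** The objective needs a before–after change per genotype or haplotype group, with covariates. One-way ANOVA and Kruskal–Wallis compare categories, without covariates. The regression uses each subject's own change with covariates, so an adjusted mean change per genotype can be estimated from it. Its stated use is to test the coefficients of the genotype categories, which is the between-group question.

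**The case against.** Several stronger readings are tempting, and the text does not support them.

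- *Pairing is ignored.* A reader might take the within-factor wording to mean before against after. The preceding sentence defines the factors as the SNPs, so the natural meaning is across the genotype categories of one SNP. Those are independent groups: a one-way ANOVA of changes across 71/70/17 held 0.0498 in simulation. No inflated standard error follows.
- *The objective is served only by unadjusted tests.* The next paragraph specifies an adjusted regression on each subject's own change, with cluster-robust errors.
- *The scale is a coin-flip.* The rejection rates above range from about a quarter to certainty, depending on skewness.
- *Genotypes will be compared by which one reaches significance.* The plan never proposes this; it tests the genotype coefficients.
- *The crude tests contradict the promise that all analyses are adjusted.* That promise stands in the regression paragraph and can fairly be read as covering the regression, with the crude tests as a preliminary step.

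It can also be said that the 39% does not describe the primary analysis. That is right: in the unadjusted step a skewed variable goes to Kruskal–Wallis, and the log-change regression for 25(OH)D3 includes its baseline.

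Finally, a condensed article may leave a per-genotype estimate to a fuller document. That tempers the second problem but not the first, because the log rule is stated outright.

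**Conclusion.** The point holds in a limited form. The stated rule lets a normality test choose both the crude test and the scale of the regression response. The consequence is small for 25(OH)D3, where rejection stays near 5% on both scales once baseline is in the model on the response's scale. It can be material for the 18 outcomes without their own baseline as a covariate. The contrast of 39% with 5% is illustrative: it rests on assumed baseline, rise, spread and allele shift, and needs baseline to differ by genotype. The Shapiro–Wilk rates assume a 5% level and gamma or lognormal shapes.

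Separately, the named within-factor tests do not match the adjusted within-group comparison in the primary objective, and the regression that could supply it is not assigned to it. This is a gap between objective and method, not evidence that an invalid test is planned. Both should be corrected before analysis.

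**What to change.** 1. State the scale of each outcome in advance: for example, 25(OH)D3 as absolute change, and right-skewed markers such as IL6, hs-CRP and MMP9 as log change.
2. Replace the Shapiro–Wilk switch with a check of model residuals.
3. Say that adjusted mean changes with 95% confidence intervals within each genotype, and the contrasts between genotypes, come from the same adjusted regression on change. Base any claim of differential response on the between-genotype test, and state the equivalent for haplotypes.
4. Keep one-way ANOVA and Kruskal–Wallis as descriptive only.

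Listing each marker's own baseline in its model would be a useful addition: in the illustration it removed the dependence on scale.

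The cost is wording; no new data or visits are needed. The downside is that a pre-set scale may fit a few markers less well, which a sensitivity analysis on the other scale covers.

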### Secondary objective

To compare inflammatory, oxidative stress, and metabolic biomarkers, biomarkers associated with cell proliferation, differentiation, damage, apoptosis, and anthropometric measures within and between polymorphic groups (Fok1, Bsm1, Taq1, Apa1, and Cdx2) in breast cancer survivors, adjusted for potential confounders**.**To compare inflammatory, oxidative stress, and metabolic biomarkers, biomarkers associated with cell proliferation, differentiation, damage, apoptosis, and anthropometric measures within and between haplotype groups in breast cancer survivors adjusted for potential confounders.To perform an investigational analysis of mean changes in inflammatory, oxidative stress, and metabolic biomarkers, biomarkers associated with cell proliferation, differentiation, damage, apoptosis, and anthropometric measures based on VDR single-nucleotide polymorphisms (SNPs), i.e., Fok1, Bsm1, Taq1, Apa1, and Cdx2.

To perform an investigational analysis of mean changes in inflammatory, oxidative stress, and metabolic biomarkers, biomarkers associated with cell proliferation, differentiation, damage, apoptosis, and anthropometric measures in different haplotype groups.

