### Sample size calculation

Sample size will be calculated by Epi Info software, using the following formula and assumption (Fig. 1). We will have 55 subjects per treatment group. Considering the third polymorphic category and the 20% dropout rate during 12 weeks, 198 subjects will be recruited.

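### Of the 19 change-score regressions, 18 do not name the outcome's own baseline as a covariate, which costs precision and leaves chance baseline imbalance between genotype groups uncorrected

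*Protocol article*

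**What the plan says.** The Statistical analyses section fixes the form of the outcome, the model and the covariates.

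- Outcome: after log-transforming non-normal variables, the investigators will "compute the differences for all response variables" between the second and the baseline measurement. The list is "25(OH)D3, BMI, WC, HC, fat mass, TNFα, IL6, hs-CRP, PAI-1, Bcl2, SOD, TAC, MDA, 8-OHdG, MMP9, IFNβ, E-cadherin, sICAM, and sVCAM", which is 19 variables: 25(OH)D3 and 18 others.
- Model: "To assess the effect of each category of exposures on outcomes of interest, we will use multiple linear regression".
- Covariates: "All analyses will be adjusted for potential confounders, including energy, fat, carbohydrate and protein intakes, physical activity, sun exposure, and 25(OH)D3 at baseline". This one set serves every outcome, and 25(OH)D3 is the only biomarker whose baseline it names.
- Standard errors: "we will use cluster robust standard errors because of repeated measurements on each subject".

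The focus on change matches the Secondary objective section, which plans "To perform an investigational analysis of mean changes in inflammatory, oxidative stress, and metabolic biomarkers" and the other marker groups, by SNP and by haplotype.

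**The concern.** A change score is usually negatively correlated with its own starting value: subjects who start high tend to fall and those who start low tend to rise, whatever their genotype. The own baseline is therefore usually a strong predictor of change, and here it is measured in everyone. The plan uses it for 25(OH)D3, where regressing change on own baseline gives the same genotype contrast as regressing the 12-week value on baseline. For TNFα, IL6, hs-CRP, MDA and the rest it adjusts for the baseline of a different biomarker and gives no reason.

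Two things are at stake for the secondary genotype comparisons. One is precision, in a study whose Discussion already concedes limited power. The other is how to read a particular result when a small genotype group happens to start higher or lower than the others. Cluster-robust standard errors address neither: one difference per subject is one row per subject, and the option changes the standard error, not the contrast.

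**Working it through.** **Sample size and cell sizes.** The Sample size calculation section states "We will have 55 subjects per treatment group" and "Considering the third polymorphic category and the 20% dropout rate during 12 weeks, 198 subjects will be recruited". This reproduces: 3 × 55 = 165 and 165 × 1.20 = 198. The 55 itself cannot be rebuilt, because its inputs are in a figure that is not shown. A 20% loss from 198 leaves about 158, so completers are taken as 158–165.

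The article gives a Fok1 minor allele frequency of 0.3285. Under Hardy–Weinberg (assumed), minor homozygotes are 0.3285² = 10.8%, which is 17.1 of 158 or 17.8 of 165. Major homozygotes are 0.6715² = 45.1%, which is 71.2 or 74.4.

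**Precision.** Let ρ be the correlation between baseline and follow-up on the analysis scale, with equal variance σ² at both times.

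- Variance of the change: 2σ²(1 − ρ)
- Residual variance after own-baseline adjustment: σ²(1 − ρ²)
- Ratio, adjusted to planned: (1 + ρ)/2

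The article gives no ρ, so a range is shown.

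| ρ (assumed) | Variance ratio (1+ρ)/2 | Planned SE larger by | Equivalent extra patients, 2/(1+ρ) − 1 | Share of baseline gap carried, 1 − ρ |
|---|---|---|---|---|
| 0.3 | 0.65 | 24.0% | 54% | 0.70 |
| 0.5 | 0.75 | 15.5% | 33% | 0.50 |
| 0.7 | 0.85 | 8.5% | 18% | 0.30 |
| 0.9 | 0.95 | 2.6% | 5% | 0.10 |
| 0.95 | 0.975 | 1.3% | 3% | 0.05 |

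**Does baseline 25(OH)D3 make up for it?** A simulation used 165 subjects, Fok1 groups at the stated allele frequency, and baseline 25(OH)D3 in both models, correlated 0 to 0.4 with the outcome's baseline. The variance ratio was 0.73–0.78 at ρ = 0.5, 0.84–0.87 at ρ = 0.7 and 0.95–0.96 at ρ = 0.9. The named covariate recovers little of the loss.

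**Chance imbalance.** For 17 against 71 subjects, the SE of a baseline gap is √(1/17 + 1/71) = 0.27 SD, so a gap of 0.25 SD is ordinary. It moves the change contrast by 0.25 × (1 − ρ): 0.175 SD at ρ = 0.3 and 0.075 SD at ρ = 0.7. The SE of the change contrast is 0.27 × √(2(1 − ρ)): 0.32 and 0.21 SD. The shift is therefore about 0.55 and 0.36 of one SE.

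In the simulation the planned contrast moved by −0.43 to −0.53 SD per SD of imbalance at ρ = 0.5, by −0.26 to −0.31 at ρ = 0.7 and by −0.08 to −0.11 at ρ = 0.9. With own baseline added, the movement was between −0.03 and 0.01. With no true baseline difference, the planned contrast averaged within 0.006 SD of zero.

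**When genotype truly shifts baseline.** Take a stable shift of 0.5 SD at both visits, no difference in response, and ρ = 0.6. The change score estimates 0.00. The own-baseline model estimates 0.5 × (1 − 0.6) = 0.20, and the simulation gave 0.203.

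**The case against.** A reader might infer that regression to the mean biases the planned comparisons or produces false findings of differential response. The article does not support that. With no true baseline difference the change-score contrast is unbiased, and chance imbalance is already part of its sampling variance, so type I error is not inflated. The shifts computed above are about half an SE or less. Nor does skewness in markers such as IL6 or hs-CRP make matters worse in itself, since the plan log-transforms non-normal variables. A claim that every secondary comparison suffers materially would also go too far: BMI and the waist and hip circumferences are likely to have high ρ and would lose 1–3% in SE.

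The strongest counter-argument is that genotype is not randomised. The Background says that VDR regulates genes involved in growth, apoptosis and inflammation, so stable genotype differences in baseline markers are plausible. Own-baseline adjustment then answers a different question and can show a difference in response where the change score shows none (0.20 against 0.00 above). Change is a legitimate target given the stated objectives. This stands, and it limits the remedy: adjustment cannot simply replace the change score.

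The covariate list is also formally open, because it is introduced as examples. That softens the point, but the article does name one biomarker baseline for all analyses, and for 18 outcomes it is not their own. This is a stated method rather than detail left to an unseen analysis plan. The absence of baseline BMI is weaker still: under an open list it is a preference.

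**Conclusion.** The point holds as a matter of precision and of conditional interpretation, for secondary outcomes only. For variable biomarkers the planned SE is about 8–24% larger than necessary, if ρ lies between 0.7 and 0.3 and variances are similar at both visits. For stable anthropometric measures the loss is negligible. Conditional on a chance baseline gap, a fraction 1 − ρ of it appears as a difference in response, and gaps of a quarter SD are to be expected with 17–18 Fok1 minor homozygotes. The primary outcome is unaffected because its own baseline is already in the model, and treating the secondary outcomes the same way is coherent. It should be changed, but it does not threaten the validity of the planned tests.

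**What to change.** For each secondary outcome, name its own baseline, on the same (log) scale as the response, as a covariate in both the SNP regressions and the haplotype regressions. Keep baseline 25(OH)D3 and the other listed covariates. Baseline BMI may be added as an optional analysis covariate.

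State which quantity is targeted: the difference in response between genotypes at equal starting level, or the difference in mean change. Report the change-score model without own baseline as a sensitivity analysis, and where the two disagree, examine whether genotype is associated with the baseline level of that marker.

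The cost is one or two more covariates per model and a second set of secondary results to report. All the measurements are already planned.
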